## SCHEMATIC DIAGRAM OF RECRUITMENT, RANDOMIZATION & TREATMENT

[figure not shown]

# 1. INTRODUCTION

## 1.1. Background

Chronic, non-healing wounds e.g. diabetic foot ulcers (DFU) are a common worldwide health problem that have substantial medical and socioeconomic importance and represent a major unmet clinical need [1]. In Europe, 1-1.5% of the population has a problem wound at any one time. The average cost per episode is 6,650€ for leg ulcers and 10,000€ for foot ulcers, accounting for 2-4% of the healthcare budget and likely to escalate with an increasingly elderly and diabetic population [2]. In the Leeds/Bradford region the overall prevalence of wounds is 2.8-3.6 people per 1000 population [3], up to 50% of which are chronically inflamed, non-healing wounds. Costs for wound care in the UK are estimated at £2.03-3.8 million per 100,000 population [4] and diabetes currently accounts for approximately 10% of the total health resource expenditure and is projected to account for around 17% in 2035/2036 [5].

The profound atrophogenic effects of glucocorticoids (GC) on human skin structure and function are well documented, causing decreased collagen content, increased transepidermal water loss (TEWL), dermal and epidermal thinning, telangiectasia, impaired wound healing (WH) and increased infection risk [6-13]. Keratinocytes, melanocytes, fibroblasts and sebocytes play significant roles as GC targets in these processes [11, 14]. These effects arise from GC excess including systemic [7, 8] and topical [10] GC therapy, Cushing's disease [6] and psychological stress [13, 15-17].

Targeting 11 $\beta$ -HSD1 through selective inhibitors has been a focus of major pharma for the last 5 years. In 2011, 11 $\beta$ -HSD1 was cited as the second most popular therapeutic target for patents filed ([www.thomsonreuters.com/content/science/pdf/ls/iyc2011.pdf](http://www.thomsonreuters.com/content/science/pdf/ls/iyc2011.pdf)), the main target indication being metabolic syndrome to reduce hepatic gluconeogenesis, steatosis and visceral adipogenesis. Proof of concept was established in a number of phase II studies but effect size may prevent progression to phase III [31-34]. Selective 11 $\beta$ -HSD1 inhibitors, such as AZD4017, are now being released for repurposing studies funded through schemes such as the MRC Asset Sharing Initiative. **The ability of systemic 11 $\beta$ -HSD1 inhibitors to target enzyme activity in peripheral tissue (e.g. skin) in man is unknown.**

Our proposed pilot trial will generate efficacy, safety and study feasibility data for the application of selective 11 $\beta$ -HSD1 inhibitors as novel therapies to improve skin function and WH in diabetes. Our skin-specific study variables are a combination of validated disease-related outcomes and **measures previously unexplored in T2DM** that will greatly improve our knowledge of GC metabolism in skin. The potential to accelerate WH in patients with T2DM would contribute to a significant **improvement in patient quality of life and reduction in costs of care.**

## 1.2. Investigational medicinal product (IMP)

### 1.2.1. Investigator brochure (IB) updates

Please refer to the current IB (edition 9 Oct 2016) for more information.

### 1.2.2. Summary of product characteristics

Not applicable

### 1.2.3. Non IMP(s)

A placebo tablet containing microcrystalline cellulose and sodium stearyl fumarate is also available to match the active tablets in size, shape and colour. Matched placebo tablets will be provided by AstraZeneca.

## 1.3. Rationale for the proposed study

The project is well-aligned with the research strategies of the School of Medicine at the University of Leeds and compliments a key platform of the Leeds Institute of Rheumatic and Musculoskeletal Medicine: Regeneration and Repair. This preliminary study aims to investigate efficacy and safety of 11 $\beta$ -HSD1 inhibition on skin function in patients with

T2DM. Study feasibility will also be assessed; if successful, data from this pilot study will inform power calculations for a future trial to investigate the ability of 11 $\beta$ -HSD1 inhibition to promote foot ulcer healing in T2DM.

## **2. STUDY AIM AND OBJECTIVES**

### **2.1. Study aims**

To evaluate efficacy of oral AZD4017 in skin, determine safety of AZD4017 in patients with T2DM, examine effects of AZD4017 on skin function and assess study feasibility.

### **2.2. Primary objective**

Evaluate AZD4017 efficacy

### **2.3. Secondary objectives**

- 1) Evaluate safety of AZD4017
- 2) Examine effects of AZD4017 on skin function
- 3) Assess study feasibility

## **3. STUDY ENDPOINTS**

### **3.1. Primary endpoint**

24 hour 11 $\beta$ -HSD1 activity in skin (efficacy) at baseline and day 28

### **3.2. Secondary endpoints**

Systemic 11 $\beta$ -HSD1 activity at baseline and day 35 and AZD4017 quantification in skin at day 28 and plasma at day 35 (to support efficacy), safety variables at baseline and days 7, 28 and 35, blood pressure, blood safety variables, ECG and biopsy inspection at day 42, urinary cortisol to cortisone metabolite analysis at baseline and day 35 (to assess systemic GC levels), skin function variables at baseline and days 2, 7, 28, 30 and 35 and feasibility variables at throughout the study.

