### Safety

- Body mass index (BMI)
- Waist-hip ratio
- Blood pressure (BP)
- Blood HbA1c
- Blood lipids
- Full blood count (FBC)
- Liver function test (LFT)
- Estimated glomerular filtration rate (eGFR)
- Kidney function test (U+E)
- Adrenal function (testosterone and dehydroepiandrosterone sulphate)
- Thyroid function
- Adverse event (AE) reporting
- Number of patients discontinuing study therapy due to safety

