#### **6.5. Withdrawal criteria**

Participants are at any time free to withdraw from study (IMP and assessments), without prejudice to further treatment (withdrawal of consent) at any point. Such participants will always be asked about the reason(s) and the presence of any AE. Participants are not under obligation to give a reason for withdrawal. If possible, they will be invited to attend a follow-up visit, ideally, at least 7 days after stopping the IMP. They will undergo the follow-up visit safety measurements and be formally discharged by telephone. Any AE will be followed up wherever possible and all remaining IMP should be returned by the participant.

Should the participant need to be withdrawn from the active treatment phase of the study between study visits for safety reasons e.g. serious adverse event (SAE) or laboratory abnormalities, study medication will be stopped immediately. If withdrawn from IMP, participants will be free to complete the remaining protocol if they choose to do so unless deemed clinically unfit by the CI, in which case they will be withdrawn from the remainder of the protocol.

IMP withdrawal criteria are as follows:

- 1) Participant decision. The subject is at any time free to discontinue treatment, without prejudice to further treatment
- 2) The participant has a clinically significant or serious AE that would not be consistent with treatment continuation, as determined by the CI or the participant; including but not limited to hospitalisation or disability, requirement for medical or surgical intervention to prevent

hospitalisation or disability; or abnormalities of liver, muscle or thyroid function that are considered unacceptable by the CI

3) Hepatotoxicity: ALT and/or ALP and/or AST >2.5x ULN or bilirubin >2x ULN. This is in keeping with Common Terminology Criteria for AE (v5.0) Grade 2 recommendations from the National Institute of Health.

4) Renal toxicity: eGFR <45

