#### 9.2.2.4. Blood pressure

Blood pressure is usually expressed in terms of the systolic (maximum) pressure over diastolic (minimum) pressure and is measured in millimeters of mercury (mm Hg) via a non-invasive sphygmomanometer. Measurements will be conducted at screening, Visits 1, 6 and follow-up by a qualified member of staff who has signed/dated the staff delegation log and recorded directly into the CRF.

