## 10. STUDY PROCEDURES BY VISIT

### 10.1. Summary schedule of study assessments

Table 1. Summary schedule of study assessments

| Assessment (day)                   | Screening (-7 to -2) | Visit 1 (0) | Visit 2 (2) | Visit 3 (7) | Visit 4 (28) | Visit 5 (30) | Visit 6 (35) | Follow-up (>42) |
|------------------------------------|----------------------|-------------|-------------|-------------|--------------|--------------|--------------|-----------------|
| Eligibility                        | X                    |             |             |             |              |              |              |                 |
| Informed consent*                  | X                    | X           |             |             | X            |              |              |                 |
| ECG                                | X                    |             |             |             |              |              |              | X               |
| BMI, BP, waist-hip ratio           | BP only              | X           |             |             |              |              | X            | BP only         |
| Blood tests**                      | X                    | X           |             | X           | X            |              | X            | X               |
| 24 hour urine collection           |                      | X           |             |             |              |              | X            |                 |
| Skin hydration                     |                      | X           |             |             |              |              | X            |                 |
| Barrier function                   |                      | X           | X           | X           | X            | X            | X            |                 |
| Barrier recovery                   |                      | X           | X           | X           | X            | X            | X            |                 |
| Skin integrity                     |                      | X           |             |             | X            |              |              |                 |
| Sudomotor test                     |                      | X           |             |             |              |              | X            |                 |
| Biobank serum and plasma           |                      | X           |             |             |              |              | X            |                 |

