**10.5. Visit 3 (day 7) at CAH LMBRU**

We will monitor the biopsy site and participants will be asked if anything has changed since the previous visit and if they have experiences any AE. Measures will be conducted as follows: 1) epidermal barrier function 2) 7 day barrier recovery time-point 3) blood samples for HbA1c, lipids, FBC, LFT, eGFR, U+E, thyroid and adrenal function 4) biopsy site inspection and wound imaging by OCT 5) compliance monitoring 6) payment

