**10.6. Visit 4 (day 28) at SJUH Diabetes Clinic**

We will monitor the biopsy site and participants will be asked if anything has changed since the previous visit and if they have experiences any AE. Biopsy sites will be inspected and measures will be conducted as follows 1) epidermal barrier function and integrity 2) blood samples for HbA1c, lipids, FBC, LFT, eGFR, U+E, thyroid and adrenal function 3) collection of IMP from pharmacy 4) obtain biopsy informed consent 5) 3 x 3mm biopsies for 11 $\beta$ -HSD1 activity, RNA-seq and AZD4017 quantification 6) 3 hour barrier recovery time-point 7) compliance monitoring 8) payment

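### Day 35 is the only scheduled on-treatment blood pressure, while section 3.2 and the synopsis, read literally, also place it at days 7 and 28

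*Protocol*

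**What the plan says.** Section 4.2 lists BP, BMI and waist-hip ratio among the safety variables. Section 3.2 gives the timing as "safety variables at baseline and days 7, 28 and 35, blood pressure, blood safety variables, ECG and biopsy inspection at day 42". The opening words of that clause, "safety variables at baseline and days 7, 28 and 35", also stand in the synopsis.

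The operational sections give a different timing for BP and agree with one another:

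- Section 9.2.2.4: "Measurements will be conducted at screening, Visits 1, 6 and follow-up by a qualified member of staff".
- Table 1 (section 10.1): the row "BMI, BP, waist-hip ratio" is marked at Visit 1 and Visit 6, with BP alone at screening and follow-up. It is blank at Visits 2 to 5.
- Section 10.5 (day 7) lists "7 day barrier recovery time-point 3) blood samples for HbA1c, lipids, FBC, LFT, eGFR, U+E, thyroid and adrenal function" and no BP.
- Section 10.6 (day 28) lists "epidermal barrier function and integrity 2) blood samples for HbA1c, lipids, FBC, LFT, eGFR, U+E, thyroid and adrenal function" and no BP.
- Section 10.8 (day 35) includes BP.

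Under section 6.5, a participant withdrawn from the drug may continue the remaining visits unless judged clinically unfit. A participant who leaves the study is invited to a visit, ideally at least 7 days after stopping: "They will undergo the follow-up visit safety measurements and be formally discharged by telephone".

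Section 13.4.2.2 plans unadjusted and adjusted between-group differences in BP, with 90% confidence intervals, in all patients who received any treatment.

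**The concern.** There are two layers. The first is textual: the endpoint section and the synopsis name the whole class of safety variables at days 7, 28 and 35, and three members of that class (BP, BMI and waist-hip ratio) are not measured at days 7 and 28.

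The second is a design matter and does not depend on how section 3.2 is read. Each patient has one scheduled on-treatment BP, at the end of dosing. A patient who stops drug earlier is next measured off drug, either at Visit 6 or at the post-withdrawal visit. Section 5.3 states that AZD4017 has not been tested in type 2 diabetes and names BP among the validated safety variables for that population. Patients who stop because of an adverse event could be informative about a BP effect, and the plan holds no on-drug reading for them. The interim safety review in section 13.8, after 8 patients have reached day 35 or been withdrawn, would likewise see at most one on-drug BP per patient.

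**Working it through.** **1. The plan's own figure.** Section 13.9 wants 12 completers per arm and allows 20% drop-out: 12 / 0.8 = 15 per arm, 30 in total. This reproduces.

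**2. Counting on-treatment BP readings.**

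| Day | Sections 3.2 and synopsis, read literally | Section 9.2.2.4, Table 1, visit lists |
|---|---|---|
| 0 (baseline) | yes | yes |
| 7 | yes | no |
| 28 | yes | no |
| 35 | yes | yes |
| 42 onwards | yes (3.2 only) | yes |

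The literal reading gives three on-treatment readings; the schedule gives one.

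**3. Patients without an on-drug reading.** The protocol gives no rate of stopping the drug. If, purely for illustration, the whole 20% allowance were early stopping of drug, that would be 0.2 × 15 = 3 per arm, or 6 of 30.

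**4. Precision.** The protocol gives no SD for BP. Assumptions: a within-patient, between-visit SD (sw) of 7 to 11 mmHg, 12 patients per arm with complete data, independent visit-to-visit errors, one baseline reading, and a treatment effect roughly constant from day 7.

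For change from baseline to the mean of m on-treatment readings:

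- SD(change) = sw × √(1 + 1/m), which is sw × √2 for m = 1 and sw × √(4/3) for m = 3.
- 90% CI half-width for the arm difference = t(0.95, 22 df) × √(2/12) × SD(change) = 1.717 × 0.408 × SD(change).

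| sw (mmHg) | One reading (day 35) | Mean of three (days 7, 28, 35) |
|---|---|---|
| 7 | 6.9 | 5.7 |
| 9 | 8.9 | 7.3 |
| 11 | 10.9 | 8.9 |

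The ratio is √(4/3) / √2 = 0.816, so the interval is about 18% narrower.

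**5. Cross-check with adjustment for baseline BP.** Half-width = t(0.95, 21 df) × SD × √(2/12) × √((1 + (m − 1)r)/m − r²), with an assumed SD of 10 to 20 mmHg and an assumed correlation r between visits of 0.4 to 0.8. The half-width falls from 4.2–12.9 mmHg (m = 1) to 3.3–9.3 mmHg (m = 3), which is 21% to 28% narrower. The 18% is therefore the more cautious figure.

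**The case against.** The strongest reply is that section 3.2 pools the days on which any variable of a class is measured. The same sentence gives skin function as baseline and days 2, 7, 28, 30 and 35, although hydration, sudomotor function and skin thickness are measured only at Visits 1 and 6. Bloods are taken at days 7, 28 and 35, so the safety clause is true on the pooled reading. The operational sections agree with each other, so site staff face no ambiguity. This stands. A reader might infer that the BP endpoint cannot be produced; the documents do not support that. No section names BP itself at day 7 or 28, and where section 3.2 does name it, at day 42, the reading is scheduled.

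A reader might also infer that 3 of 15 per arm will have no on-drug BP, or that early stoppers drop out of the BP analysis. Neither follows. The 20% is an allowance for not completing the protocol, not a forecast of stopping drug. Section 6.5 lets those withdrawn from drug stay in the visits, and the planned safety analysis includes everyone treated, so those who attend Visit 6 contribute an off-drug day-35 value.

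Finally, the trial is descriptive, section 5.3 reports no clinically relevant vital-sign changes in earlier studies, and adverse events are assessed at every visit. One baseline and one end-of-treatment BP is a defensible pilot choice. The sample size, not the number of readings, is the main reason for the wide interval, and averaging over days 7 to 35 estimates a different quantity from the day-35 difference. These points limit the claim. They do not alter the fact that only one on-treatment BP is scheduled.

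**Conclusion.** The point holds in a limited form. The endpoint wording in section 3.2 and the synopsis does not match the BP, BMI and waist-hip schedule and should be reconciled; it is a wording conflict. The design limitation holds on either reading: day 35 is the only scheduled on-treatment BP, and anyone stopping drug earlier has no on-drug value. How many patients that affects cannot be read from the protocol.

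The gain in precision from two more readings is modest, about 18% (6.9–10.9 down to 5.7–8.9 mmHg). It rests on the assumed within-patient SD, 12 complete patients per arm and a roughly constant effect from day 7. Patients stopping before day 7 would still have no on-drug BP. The change is worth making because it is cheap and BP is a named safety variable in the first use of this drug in this population.

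**What to change.** Reconcile section 3.2 and the synopsis with section 9.2.2.4 and Table 1, by one of two routes.

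- **Preferred:** add BP to the Visit 3 and Visit 4 lists (sections 10.5 and 10.6), Table 1 and section 9.2.2.4. Present the day-7, day-28 and mean on-treatment BP differences as supplements, keeping the day-35 comparison as planned. BMI and waist-hip ratio can be limited to baseline and day 35 in section 3.2 and the synopsis.
- **Otherwise:** limit BP, BMI and waist-hip ratio in section 3.2 and the synopsis to baseline and day 35, with day 42 kept for BP, and state that patients who stop drug before day 35 have no on-drug BP.

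The preferred route costs two short cuff readings per patient, at visits already attended and at locations where BP is already taken, plus the text changes. The other route costs wording only.

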## **4. STUDY VARIABLES**

### **4.1. Primary variable**

#### **AZD4017 efficacy**

- 24 hour 11 $\beta$ -HSD1 activity in skin

## 4.2. Secondary variables

### AZD4017 efficacy

- 24 hour urinary cortisol to cortisone metabolite ratio
- AZD4017 levels in skin and plasma

### Safety

- Body mass index (BMI)
- Waist-hip ratio
- Blood pressure (BP)
- Blood HbA1c
- Blood lipids
- Full blood count (FBC)
- Liver function test (LFT)
- Estimated glomerular filtration rate (eGFR)
- Kidney function test (U+E)
- Adrenal function (testosterone and dehydroepiandrosterone sulphate)
- Thyroid function
- Adverse event (AE) reporting
- Number of patients discontinuing study therapy due to safety

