#### **6.5.2. Managing/replacing patients who withdraw early**

Participants who decide to withdraw will be invited to complete a withdrawal form which will be stored in the TMF (although refusal to do so will be respected). Participants who are withdrawn by the CI will be recorded in a Withdrawal Log that documents the enrolment number, participant initials, reason(s) for withdrawal and treatment offered (if applicable). A copy of the log will be retained in the CRF which will also directly capture information on withdrawal outcome (Discontinuation due to Adverse Event or Elective Withdrawal). Withdrawal Log originals will be stored in the TMF. Participants who withdraw or are withdrawn pre-randomization will be classified as screening failures (see section 6.3.4). Participants who withdraw or are withdrawn post-randomization (see section 6.5) will be classified as withdrawals and will not be replaced.

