### **9.2.2. Safety**

AE-related participant withdrawals (i.e. number of Discontinuations due to Adverse Events) e.g. exceeding hepatic/renal stopping criteria, myocardial infarction or stroke, inpatient hospitalization or any other AE deemed by the clinical care team to require trial withdrawal will be recorded as a Discontinuation due to Adverse Event under withdrawal outcome in the CRF. The following safety measures will also be used to assess AZD4017 safety:

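### Stopping study drug for safety is captured as withdrawal, so a patient who stops the drug but stays in the trial may not be counted

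*Protocol*

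**What the plan says.** Section 4.2 (Safety) names the variable as "Number of patients discontinuing study therapy due to safety".

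Section 9.2.2 turns it into "AE-related participant withdrawals (i.e. number of Discontinuations due to Adverse Events". Its examples begin with "exceeding hepatic/renal stopping criteria", go on to myocardial infarction, stroke and inpatient hospitalisation, and end with a general clause for further events: "AE deemed by the clinical care team to require trial withdrawal will be recorded as a Discontinuation due to Adverse Event under withdrawal outcome".

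Section 6.5 treats leaving the drug and leaving the study as different events. The hepatic and renal limits appear there in the list of criteria for withdrawal from IMP. So does a wider criterion for clinically significant or serious adverse events, which mentions muscle and thyroid abnormalities. On what follows, it says: "If withdrawn from IMP, participants will be free to complete the remaining protocol if they choose to do so", unless the chief investigator judges them clinically unfit.

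Section 6.5.2 says the CRF captures "withdrawal outcome (Discontinuation due to Adverse Event or Elective Withdrawal"), and adds: "Participants who withdraw or are withdrawn post-randomization (see section 6.5) will be classified as withdrawals and will not be replaced".

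The retention item in section 4.2 (Feasibility) has two parts. One is the number who complete the final assessment. The other is the reasons for discontinuation with a count for each; it does not say whether the drug or the trial is meant.

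**The concern.** The variable concerns the drug, but the rule for collecting it is worded in terms of leaving the trial. The two agree only if everyone who stops the drug for safety also leaves, and section 6.5 provides for the opposite.

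Two things are at stake. The first is completeness of a named safety variable. Evaluating safety is the first secondary objective, and section 5.3 notes that AZD4017 has not been tested in patients with type 2 diabetes. The second is the table of discontinuations by reason, part of the feasibility data meant to inform a later trial. If a drug stop with full follow-up and a trial exit share one label, that table cannot be read as either.

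The stop date and reason should be collected as the event happens. If the CRF does not ask for them, the analysis may be unable to recover them.

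**Working it through.** **The plan's own figures.** Sections 6.2 and 13.9 give 12 completers per arm and 20% drop-out: 12 / (1 − 0.20) = 15 per arm, and 30 × 0.80 = 24 completers. Both reproduce, and nothing here changes them.

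**The sections side by side.** Consider patients who stop the drug for safety:

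| Patient | Counts under 4.2? | Entered if 9.2.2 is followed literally? | Completes final assessment? |
|---|---|---|---|
| Exceeds a hepatic or renal limit, stays | Yes | Yes, named | Yes |
| Has another event named in 9.2.2, stays | Yes | Yes, named | Yes |
| Stops for a different adverse event (for example muscle or thyroid, section 6.5 criterion 2) that does not require leaving, stays | Yes | No clear place | Yes |
| Leaves the trial because of an adverse event | Yes | Yes | No |

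The gap is the third row. The first two rows show a different difficulty: these patients are entered under a withdrawal heading although section 6.5 lets them stay, so the field does not tell drug stop from trial exit. The wording of the general clause in 9.2.2 also suggests that the named events require leaving the trial, which section 6.5 does not say.

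**Size of an undercount.** The documents give no rate of safety stops among patients who stay, so the number m of uncounted patients in an arm is an assumption. With 15 per arm, all taking at least one dose (the safety set in section 13.4.2.2 is those who received treatment), the arm's rate is low by m/15:

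- m = 1: 1/15 = 6.7 percentage points
- m = 2: 2/15 = 13.3
- m = 3: 3/15 = 20.0

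If nobody stops the drug for an unnamed event and stays, m = 0 and there is no error.

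**Size of the mixing.** Suppose k of the 30 stop the drug for safety, all stay to the end, and all are entered under the withdrawal outcome. A reader who takes that field as trial exit sees 30 − k remaining: 29/30 (96.7%) for k = 1, 27/30 (90%) for k = 3, 24/30 (80%) for k = 6. The count by final assessment is 30/30 each time. The second count is the first retention measure in section 4.2, so it stays right; only the breakdown by reason carries the ambiguity.

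For any one patient the two effects are alternatives. If entered, the drug stop is counted but may look like a trial exit; if not entered, it is missed but no false exit appears.

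**The case against.** The strongest reply is that this is loose wording with little consequence. The hepatic and renal stops, which follow numerical limits, are explicitly entered. The list in 9.2.2 is given as examples, so a site could enter a muscle or thyroid stop as well. Section 6.5 lets either the chief investigator or the participant judge an adverse event incompatible with continued treatment, so a participant-led stop need not be coded as elective. Withdrawing participants are asked about reasons and adverse events, there is a Withdrawal Log, and tablet counts and the diary card (sections 8.8 and 12.4.1) show when dosing ceased. The CRF is not shown and may hold a separate item for stopping the drug.

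Much of this stands. It limits the undercount to a residual group and makes it possible rather than certain. It does not remove the conflict in the text. The class that 9.2.2 describes is participant withdrawal, and its general clause is tied to leaving the trial. The log in 6.5.2 covers those classed as withdrawn by the chief investigator. The tablet and diary records are not linked to this variable. Even if the CRF separates the two events, the protocol would still need to say so.

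**Conclusion.** The point holds in a limited form. Sections 4.2, 6.5, 6.5.2 and 9.2.2 do not agree on whether the safety variable counts drug stops or withdrawals. Followed literally, 9.2.2 can miss a patient who stops the drug for an adverse event it does not name and stays in the trial. The discontinuation breakdown in 4.2 can mix drug stops with trial exits. Each missed patient is worth 6.7 percentage points in an arm of 15, assuming all 15 are dosed; the number of such patients is unknown and may be zero.

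A reader might infer more than this, on three counts:

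- **That both safety stops and retention are miscounted.** The first retention measure is completion of the final assessment. It does not use the withdrawal field, and a patient off the drug who attends counts as retained.
- **That the planned 20% drop-out sizes the error at three patients per arm.** That allowance is for people who do not complete. Patients who stop the drug and stay are not among them.
- **That a collected day-28 biopsy would be treated as missing.** Section 13.4.1 includes all patients as randomised and section 13.7 deals only with missing data. Nothing there discards an observed value because the patient stopped the drug.

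**What to change.** Record two items in the CRF: permanent stop of IMP (date, reason, related to an adverse event yes or no) and end of study participation (date, reason). Count the section 4.2 safety variable from the first, and study discontinuations from the second. Keep completion of the final assessment as the main retention measure, and state in the retention item which kind of discontinuation the breakdown refers to.

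Bring the wording of 4.2, 6.5, 6.5.2 and 9.2.2 into line with this. The edit concerns recording and counting only; it should leave every stopping rule as it is.

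The cost is one added CRF item and wording changes in four sections. No visits are added, and the sample size and the primary analysis stay the same.
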